## Abstract

**Background:**

Operating room to intensive care unit handoffs are high-risk events for critically ill patients. Studies in selected patient populations show that standardizing operating room to intensive care unit handoffs improves information exchange and decreases errors. To adapt these findings to mixed surgical populations, we propose to study the implementation of a standardized operating room to intensive care unit handoff process in two intensive care units currently without an existing standard process.

**Methods/Design:**

The Handoffs and Transitions in Critical Care (HATRICC) study is a hybrid effectiveness- implementation trial of operating room to intensive care unit handoffs. We will use mixed methods to conduct a needs assessment of the current handoff process, adapt published handoff processes, and implement a new standardized handoff process in two academic intensive care units. *Needs assessment*: We will use non-participant observation to observe the current handoff process. Focus groups, interviews, and surveys of clinicians will elicit participants’ impressions about the current process. *Adaptation and implementation*: We will adapt published standardized handoff processes using the needs assessment findings. We will use small group simulation to test the new process’ feasibility. After simulation, we will incorporate the new handoff process into the clinical work of all providers in the study units. *Evaluation*: Using the same methods employed in the needs assessment phase, we will evaluate use of the new handoff process. *Data analysis*: The primary effectiveness outcome is the number of information omissions per handoff episode as compared to the pre-intervention period. Additional intervention outcomes include patient intensive care unit length of stay and intensive care unit mortality. The primary implementation outcome is acceptability of the new process. Additional implementation outcomes include feasibility, fidelity and sustainability.

**Discussion:**

The HATRICC study will examine the effectiveness and implementation of a standardized operating room to intensive care unit handoff process. Findings from this study have the potential to improve healthcare communication and outcomes for critically ill patients.

**Trial registration:**

ClinicalTrials.gov identifier: NCT02267174. Date of registration October 16, 2014.

**Electronic supplementary material:**

The online version of this article (doi:10.1186/1471-2482-14-96) contains supplementary material, which is available to authorized users.

## Background

Handoffs are transfers of patient care and accountability that are a well-recognized risk factor for adverse events in healthcare such as medication errors [1] and delays in diagnosis or treatment [2]. Handoffs are ubiquitous in medicine due to the specialization of care across providers, disciplines and care settings [3]. Despite mounting evidence that handoff standardization is beneficial [4–13], variability in handoff processes persists in all the areas associated with surgical and anesthetic practice [14]. Of particular concern is the handoff occurring for patients admitted from the operating room (OR) to the intensive care unit (ICU). This transfer is high risk because it involves physical movement of patients and multiple handoffs among providers of different disciplines (anesthetist to critical care clinician, surgeon to critical care clinician, operating room nurse to critical care nurse, *et cetera*) [15]. Also, the patients whose care is transferred are often incapacitated and thus unable to participate, making them vulnerable to error and preventable harm.

Published reports demonstrate improved information exchange [5, 7–12] and improved patient outcomes [4, 9] when *cardiac* OR-to-ICU handoffs are standardized, especially in pediatric cardiac populations [7–12]. Though the findings from this work are intriguing, it is unclear whether the approaches adopted in postoperative pediatric cardiac care apply to *all* patients requiring postoperative critical care. Heterogeneous patient groups have differing levels of acuity and different nursing needs. Additionally, a larger number of potential procedures and providers may complicate the adoption of and adherence to a standard process. The proposed project aims to adapt previously published approaches to handoff standardization and to implement a handoff process that will be applicable to the care of patients undergoing cardiac, general surgical, orthopedic, transplant, trauma, and vascular surgical procedures.

The Handoffs and Transitions in Critical Care (HATRICC) study will employ a mixed methods hybrid effectiveness-implementation design [16] to study both the implementation and effectiveness of a standard OR-to-ICU handoff process in a mixed surgical population. As Curran *et al.* discussed in their work describing hybrid study models, this study design has the potential to speed the adoption of evidence based practice by providing information on the effectiveness of interventions in real world settings while simultaneously collecting information about implementation strategies [16]. There is sufficient evidence to support a trial of handoff standardization in our study population, but we do not know whether standardization will be effective for a mixed surgical population. The procedures needed to effectively implement a standard postoperative handoff process are similarly unclear.

### Project aims and hypotheses

There are multiple surgical settings with demonstrated inadequate handoff practices: intraoperative handoffs between anesthesia providers, [17, 18] handoffs in the post-anesthesia care unit, [19] handoffs from the ICU to the OR, [20] and those from the OR to the ICU [5, 7–12]. We chose to study OR-to-ICU handoffs because the evidence base supporting handoff standardization is more established for these handoffs than for the others mentioned. The HATRICC study has three aims:Perform a needs assessment of the OR-to-ICU handoff process in two ICUs that serve mixed surgical populations.Adapt and implement a standardized OR-to-ICU handoff process.Evaluate the implementation and effectiveness of a standardized OR-to-ICU handoff process.

The project will test both intervention effectiveness and implementation hypotheses:

*Intervention effectiveness hypothesis:* After implementing a standard handoff process, the number of information omissions per handoff will decrease by 50%.

*Implementation hypothesis:* Clinician acceptance of a new standardized OR-to-ICU handoff process will be high, as assessed qualitatively.

HATRICC is based on a conceptual model that relates teamwork and communication to patient outcomes (Figure 1). In addition to addressing the three aims above, we will use study measures to test whether the relationships in this model are consistent with our observations of actual clinical practice.

**Figure 1 Fig1:**
[figure not shown]
**HATRICC conceptual model.**

## Methods/Design

HATRICC is a Type 1 hybrid effectiveness-implementation trial [16] designed to test the effectiveness of a standardized OR-to-ICU handoff process while collecting data about the implementation of this process [16]. The project is structured as a parallel mixed methods study with simultaneous collection of qualitative and quantitative data (QUAL + QUAN) during the needs assessment phase (Aim 1). We will use the findings from the needs assessment phase to adapt published handoff processes and test the proposed standard handoff process (Aim 2). We will then implement the standardized handoff, simultaneously collecting both qualitative and quantitative data (equally weighted) to evaluate the effectiveness of the intervention and gather information about the implementation strategy and of the intervention itself (Aim 3). The study draws on the Consolidated Framework for Implementation Research (CFIR), [21] which describes 5 domains to guide implementation research: (1) intervention characteristics, (2) outer setting (economic, political and social context), (3) inner setting (structural, political, cultural context of organizations), (4) individuals involved, and (5) implementation process. Most of these CFIR constructs do not have validated objective measures and thus will be explored using a grounded theory [22] approach.

The methods that we will use to achieve the study aims are detailed below, with CFIR constructs indicated in *italic typeface*.

### AIM #1: Needs assessment of the current handoff process

The OR-to-ICU handoff process involves the physical transfer of patients from the operating room to the intensive care unit as well as the transfer of patient care responsibilities. In both study hospitals, the patient is transported by an anesthetist (physician or certified registered nurse anesthetist) and a member of the surgical team (physician or physician assistant). Patients have real-time physiologic monitoring during this transfer, with heart rate and blood pressure data continuously available to the transporting clinicians who may administer medications or perform other interventions (e.g. cardiopulmonary resuscitation) as needed for life support. On arrival to the intensive care unit, physiologic monitors are transferred to the in-room monitors, patient stability is ensured, and a conversation ensues between the transmitting providers (anesthetist, surgeon) and the receiving providers (physician, nurse practitioner, registered nurse). Although handoff communication commonly takes place at the patient’s bedside, there may be additional asynchronous communication about the patient between the ICU team and members of the surgical team who are not physically present for the handoff. There are no explicit guidelines or expectations about the way that handoff communication should be conducted, but all providers involved in the patient’s physical transfer are expected to engage in the handoff in some way.

#### AIM 1 procedures

Over the course of 8–12 weeks, we will evaluate OR-to-ICU handoffs as they currently take place in two surgical intensive care units (*inner setting)* in Philadelphia, Pennsylvania (*outer setting).* Although these ICUs are part of the same health system, they serve different surgical populations and are staffed by different types of providers (*individuals involved*; Table 1). Patients receiving care in the two study units live throughout the Delaware Valley and represent a diverse payor mix (Medicaid, Medicare, private payors) as well as indigent patients receiving uncompensated care (*outer setting*).

**Table 1 Tab1:** **Study ICU characteristics**

	Study unit	
Characteristic	Study unit 1	Study unit 2
Surgical specialties represented	General, oncologic, orthopedic, otorhinolaryngologic, plastic, transplant, trauma, urologic, vascular	Cardiac, general, orthopedic, vascular
Beds	24	16
ICU model	Semi-closed*	
Clinicians	• Registered nurses	• Registered nurses
	• Attending physicians: ICU, surgery	• Attending physicians: ICU, surgery
	• Fellows: ICU, surgery	• Fellows: cardiac surgery
	• Residents: anesthesia, ICU, surgery	• Residents: anesthesia, ICU, surgery
	• Advanced practitioners: nurse practitioner	• Advanced practitioners: physician assistants, certified registered nurse anesthetists
Patient demographics	50% white, 49% black, 1% Asian, 9% other	

*“Semi-closed” indicates that each patient in the study units has two care provider teams – one surgical team and one intensive care unit team. Other models include “open” units where patients have just a surgical care provider team and “closed” units where patients have just an ICU provider team.

The needs assessment has four components:Observation of OR-to-ICU handoffs: On notification of patient arrival to the ICU, trained research staff will directly observe the OR-to-ICU handoff by audio recording the handoff and taking detailed field notes about their observations. Research staff will complete a checklist (Additional file 1) capturing elements of handoff content, team performance [10] and handoff quality [23]. Immediately after each handoff, audio recordings will be reviewed to ensure accuracy of checklist completion^a^. Then, the observers will answer open-ended prompts (Additional file 2) about the handoff to guide recording of their impressions. A subset of the handoffs will be observed by two staff members, allowing for calculation of inter-rater reliability of checklist completion. In Study Unit 1, handoffs are sometimes video recorded as part of an ongoing performance improvement project. If these recordings exist, research staff will review them to facilitate interrater calibration and to determine whether they provide additional information about the handoff process. To capture elements of handoff communication not occurring at/near the patient bedside, we will query ICU providers about other sources of patient information, such as telephone conversations and the electronic medical record. This query will be delivered as a self-administered questionnaire completed after the in-person handoff.

(2)Focused chart reviews: We will abstract the pre-, intra-, and postoperative records of each patient whose handoff is observed to enable the research team to determine the accuracy of handoff information transfer with respect to five specific content areas: past medical history, allergies, airway management, medication infusions, and intraoperative fluid balance. We chose these content areas because, to our knowledge, they are present on all published OR-to- ICU handoff checklists.(3)Event report reviews: With permission from hospital administration, the voluntary event reports of each ICU will be reviewed on a weekly basis to determine whether any reported adverse events were attributed to handoffs. Basic characteristics of any such events will be recorded as research data.(4)Focus groups, interviews, surveys: We will take several approaches to elicit the thoughts and impressions of clinicians involved in the handoff process (*individuals involved*; Table 2). *Focus groups*: Ten to twelve focus groups will be held in total; these will be evenly split between the needs assessment and evaluation phases. In study unit 1 (Table 1), we will hold separate focus groups of nurses and residents. In study unit 2, we will hold separate focus groups of nurses, residents, and certified registered nurse anesthetists. These focus groups will be led by a trained moderator from the Mixed Methods Research Laboratory at the University of Pennsylvania. The purpose of the focus groups is to elicit perceptions about the current handoff process and impressions about standardized handoffs while another member of the research team takes field notes. The focus groups will be audio recorded and professionally transcribed. *Interviews*: Nurse practitioners and physician assistants in the study ICUs will be individually interviewed because there are relatively few of them and assembling them into one focus group would be logistically challenging. The interviews will be conducted by a single investigator ([name]), who will elicit perceptions about the current handoff process and impressions about standardized handoffs. *Surveys*: There are more than 700 clinicians (Table 2) who participate in the OR-to-ICU handoff process. Given that we will be unable to observe most of these clinicians, we designed a survey to ask providers about their current experience with and attitudes about OR-to-ICU handoffs (Additional file 3). All clinicians who participate in OR-to-ICU handoffs will be invited to take this electronic, self-administered questionnaire. Survey data will be collected and managed using REDCap electronic data capture tools [24] hosted at the University of Pennsylvania.

**Table 2 Tab2:** **Eligible subjects in study population, stratified by study phase**

Study component	Recruitable population*	Target sample size
**Observation (first round)**	440 patients	40-60 patients
	366 clinicians	40-60 handoffs: each consisting of 4-6 clinicians
**Surveys (first round)**	460 clinicians:	460 clinicians
	100 OR nurses	
	100 attending physicians and fellows	
	130 ICU nurses	
	120 residents and CRNAs	
	12 NPs/PAs	
**Interviews (first round)**	12 NPs/PAs	12 NPs/PAs
**Focus groups (first round)**	130 ICU nurses	3 focus groups of 5-8 participants
		(total 15 to 24 ICU nurses)
	120 resident physicians and CRNAs	3 focus groups of 5-8 participants
		(total 15 to 24 residents/CRNAs)
**Simulations**	12 NPs/PAs	4 NPs/PAs (1 per simulation)
	120 residents	8 residents (2 per simulation)
	130 ICU nurses	8 nurses (2 per simulation)
**Observation (second round)**	440 patients	40-60 patients
	366 clinicians	40-60 handoffs consisting of 4-6 clinicians each
**Surveys (second round)**	460 clinicians:	460 clinicians
	100 OR nurses	
	100 attending physicians and fellows	
	130 ICU nurses	
	120 residents and CRNAs	
	12 NPs/PAs	
**Interviews (second round)**	12 NPs/PAs	12 NPs/PAs
**Focus groups (second round)**	130 ICU nurses	2 focus groups of 5-8 participants
		(total 10 to 16 ICU nurses)
	120 resident physicians and CRNAs	2 focus groups of 5-8 participants
		(total 10 to 16 residents/CRNAs)

*Abbreviations: CRNA* certified registered nurse anesthetist, *ICU* intensive care unit, *NP* nurse practitioner, *OR* operating room, *PA* physician assistant.

*Numbers given are estimates, as patient volume and clinician staff numbers are expected to vary over the course of the study.

#### AIM 1 measures

Aim 1 will address the question “How do OR-to-ICU handoffs occur in settings without a standardized process?” As we collect data to answer this question, we will also collect information to enable development of a standard handoff process. Given the hybrid nature of the study, we will measure concepts related to both effectiveness and implementation (Table 3). These are not true “outcomes” because they are collected at baseline, but they will enable us to detect changes occurring in the intervention phase:

**Table 3 Tab3:** **Study outcomes stratified by measure type (implementation vs. intervention) and data type (qualitative vs. quantitative)**

		Measure type	
		*Implementation*	*Intervention*
Data type	*Qualitative*	Acceptability (primary)	Handoff quality
		Appropriateness	
		Fidelity	
		Sustainability	
	*Quantitative*	Acceptability*	Information omissions, number (primary)
			Handoff accuracy
			Handoff duration
			Team members present, number
			Teamwork quality**
		Fidelity	Professionalism
			Diagnostic test utilization
			Medication orders
			Patient ICU length of stay
			Patient ICU mortality
			Patient hospital mortality

*Assessed with 5-point Likert scale.

**Assessed with 3-point scale.

Effectiveness outcome 1: Number of information omissions. Published studies demonstrate that important patient information is frequently omitted from OR-to-ICU handoff communication when these handoffs are not standardized [8, 12]. Using a data capture tool developed for this project (Additional file 1), we will determine how many data elements are absent from each handoff.

Effectiveness outcome 2: Handoff accuracy. To our knowledge, no studies to date have reported whether the information reported during OR-to-ICU handoff is actually true. As such, there are no validated measures of handoff accuracy. To attempt to determine whether OR-to-ICU handoffs are accurate, we will compare observed handoff content (for the five elements described above) to the patient’s medical record to calculate accuracy. Accuracy will be defined as the number of content areas correctly relayed during handoff divided by the number of content areas for which medical record data is available.

Additional effectiveness outcomes: We will collect data about patient outcomes, including ICU and hospital mortality as well as ICU and hospital length of stay. We will collect data about resource utilization in the first 24 hours of ICU admission (e.g. diagnostic test utilization, medications). We will also measure process outcomes such as number of team members present, handoff duration, quality of teamwork (coded on a 3-point scale), and professionalism (coded on a 3-point scale).

Implementation outcome 1: Acceptability, defined as “the perception among implementation stakeholders that a given treatment, service, practice, or innovation is agreeable, palatable, or satisfactory” [25]. We know of no validated measures of acceptability in critical care or perioperative settings. Investigators in mental health have used semi-structured interviews and questionnaires to assess acceptability [25]. For our study, we will analyze survey data and interview/focus group transcripts to qualitatively characterize acceptability of the current handoff practice and that of a proposed standardized process. Drawing on CFIR, we will explore how the inner setting of each ICU and the individuals involved impact acceptability of a standardized handoff process as well as the other implementation constructs described below.

Additional implementation outcomes: Appropriateness, defined as the “perceived fit, relevance, or compatibility” of a standardized handoff process, and feasibility, defined as the extent to which a standardized handoff process can be carried out [25]. As with “acceptability”, we will qualitatively characterize these implementation outcomes.

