**Handoff observation stratification scheme.**

Quantitative data: As the study is a Type 1 hybrid effectiveness-implementation trial, [16] power calculations are based on our effectiveness hypothesis. Previously published work suggests that, on average, 36-40% of handoff information is omitted in the absence of a standardized handoff process [7, 8]. After institution of a standardized process, information omissions drop by 50-66% [7, 8]. Our handoff observation tool has 13 content items; if our observations are consistent with published work, we will observe 4–5 omissions per handoff episode. We are assuming a standard deviation of 2 information omissions given the heterogeneity of this process, although others have reported a smaller standard deviation [7]. If these assumptions hold true, we will have 95.7% power to detect a drop in information omissions from 4.5 to 3 (a 33% drop), based on a sample size of 96 (48 pre-intervention, 48 post-intervention), and a two-tailed alpha of 0.05. The power calculation suggests that our target sample size for qualitative data will also be sufficient to detect pre- and post- intervention differences in our primary quantitative outcome (Table 3).

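### Handoff accuracy, as defined, scores an unmentioned content area the same as a wrongly reported one, so it does not isolate whether what is said at handoff is true

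*Protocol article*

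**What the plan says.** The protocol article lists handoff accuracy as effectiveness outcome 2 under AIM 1 measures. The number of omissions is the primary effectiveness outcome (Table 3). The reason given for the accuracy outcome is that, as far as the authors know, "no studies to date have reported whether the information reported during OR-to-ICU handoff is actually true".

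The formula follows in the same paragraph: accuracy is the "number of content areas correctly relayed during handoff divided by the number of content areas for which medical record data is available". The areas are set out under AIM 1 procedures, in the item on focused chart reviews: "five specific content areas: past medical history, allergies, airway management, medication infusions, and intraoperative fluid balance". That item gives the purpose of the chart abstraction as being to "determine the accuracy of handoff information transfer with respect to five specific content areas".

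Omissions are measured separately as effectiveness outcome 1, where "we will determine how many data elements are absent from each handoff". AIM 3 measures repeats both outcomes after the intervention. Nowhere does the article divide the areas that were not correctly relayed into those left out and those stated wrongly.

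**The concern.** The stated question concerns what was said: is it true? The formula's denominator is set by the chart, regardless of what was said. An area nobody mentions cannot be correctly relayed, yet it counts against accuracy just as a false statement does.

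This matters because the intervention includes a tool meant to get more information across, so it acts directly on the omission part of the ratio. If the score rises after implementation, a reader cannot tell whether staff were more often right or only said more. A loss of truthfulness, for instance if form entries were read out unchecked, could be offset by fewer omissions and go unnoticed. The areas concerned include allergies, infusions and fluid balance.

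**Working it through.** **Plan's own figure.** The article gives no expected value for accuracy. Its one power figure, for omissions, reproduces. With means 4.5 and 3, SD 2 and 48 per period, the standardised difference is 1.5 / (2 × √(2/48)) = 3.67, and power is Φ(3.67 − 1.96) ≈ 95.7%, as stated. The inputs below are therefore read as the authors used them.

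**Formula.** For one handoff, let *n* be the areas with chart data, *m* those of the *n* that are mentioned, and *c* those correctly relayed. The plan's score is c/n = (m/n) × (c/m). With omission rate *o* and truthfulness *q* (the share of mentioned areas that are true), its expected value is (1 − o) × q. The quantity the stated purpose asks about is q.

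A hypothetical pair with n = 5 shows the problem. One handoff mentions three areas, all correctly; another mentions all five, three correctly. Both score 3/5 = 60%, while truthfulness is 3/3 = 100% and 3/5 = 60%.

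**Inputs.**
- Scenario A uses the planning values under Sample size and power considerations: 4.5 to 3 omissions, where "Our handoff observation tool has 13 content items". So o goes from 4.5/13 = 34.6% to 3/13 = 23.1%.
- Scenario B uses the published rate in the same section: "on average, 36-40% of handoff information is omitted in the absence of a standardized handoff process". The midpoint is 38%, halved to 19% in line with the 50% effectiveness hypothesis.
- Assumption: these overall rates apply to the five areas. The article gives no rate for them.
- Assumption: q is between 80% and 100%. The article gives no value.

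**Truthfulness unchanged.**

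| q, both periods | A: before → after | A: change (points) | B: before → after | B: change (points) |
|---|---|---|---|---|
| 80% | 52.3% → 61.5% | +9.2 | 49.6% → 64.8% | +15.2 |
| 90% | 58.8% → 69.2% | +10.4 | 55.8% → 72.9% | +17.1 |
| 100% | 65.4% → 76.9% | +11.5 | 62.0% → 81.0% | +19.0 |

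For example, A at 90% is (1 − 4.5/13) × 0.90 = 58.8% and (1 − 3/13) × 0.90 = 69.2%. With mentioned areas as the denominator, the change is zero in every row.

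**Truthfulness falling from 95% to 80%.**
- A: (1 − 4.5/13) × 0.95 = 62.1%, then (1 − 3/13) × 0.80 = 61.5%. The score is roughly flat.
- B: 0.62 × 0.95 = 58.9%, then 0.81 × 0.80 = 64.8%. The score rises.

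**Break-even.** The score shows no change when q after = q before × (1 − o before)/(1 − o after). From 90%, that is 0.90 × 0.654/0.769 = 76.5% in A and 0.90 × 0.62/0.81 = 68.9% in B.

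**The case against.** The strongest reply is that the ratio is a legitimate measure. The chart-review item speaks of accuracy of information transfer, and the share of known facts that arrive correctly is a fair reading of that. The article says that no validated measure exists and presents this one as an attempt. The formula is stated openly, is applied the same way in both periods, and is reported alongside omissions. This stands as a defence of keeping the ratio. It does not answer the point, because the paragraph that defines the ratio justifies it by the truth of what is reported, and the ratio does not isolate that. The omission count does not let a reader recover it either: it covers the 13 tool items, not specifically the five areas.

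A reader might infer three stronger things that the article does not support.
- *Accuracy is a second copy of the primary outcome and rises whenever omissions fall.* Only omissions in the five areas with chart data move it. The observation tool (Additional file 1) is not shown, so the overlap with its 13 items cannot be checked.
- *The trial will declare a false significant improvement.* The Data analysis section plans descriptive statistics for the quantitative measures. It names Mann–Whitney tests for omissions and for site differences in acceptability and fidelity, and no test for accuracy.
- *A drop in truthfulness from 95% to 80% would still show as a gain.* That holds at 38% to 19% but not at the plan's own 4.5 to 3, where the score is flat.

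It is also fair to say that a mentioned-only denominator has a weakness of its own. The intervention may change which areas get mentioned, so the before and after figures need not compare like with like.

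**Conclusion.** The point holds as a mismatch between the stated purpose of a secondary outcome and its formula. The direction follows from the formula alone: with truthfulness above zero and unchanged, fewer omissions among the five areas raise the score. The size is illustrative: 9 to 12 points at the planning values and 15 to 19 points for 38% to 19%. Both ranges rest on applying the overall omission rate to the five areas and on truthfulness of 80-100%. The five areas were chosen because the authors believe they appear on all published checklists, so their omission rate may differ from the overall one.

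The ratio always blunts a fall in truthfulness that comes with fewer omissions in these areas; whether it hides the fall completely depends on the two rates. The primary outcome, its test and its power are unaffected. The definition should be corrected because the remedy is cheap, but it does not threaten the trial's main conclusion.

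**What to change.** Classify each of the five areas with medical record data, in each handoff, as correct, incorrect or omitted, and tabulate all three by period. Then report two measures:

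1. Accuracy of what was reported: correct / (correct + incorrect), pooled over handoffs so that those mentioning few areas do not dominate and those mentioning none cause no undefined values. Show it by content area as well, so that a change in the mix of mentioned areas is visible.
2. The present ratio, kept unchanged but under a label such as *complete and correct transfer*.

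The cost is a few sentences of protocol wording. The present numerator already requires a decision on whether each area was correctly relayed; the change splits the remainder into incorrect and omitted. The planned checklist, audio review and chart abstraction appear to supply what is needed. The downside is that the mentioned-only denominator is smaller, varies between handoffs and depends on what staff choose to mention. The two measures should therefore be read together, and neither should replace the other.
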